#### Trial Feasibility Outcomes

The primary outcomes for trial feasibility include the rates of screening, eligibility, enrollment, and retention. The secondary outcomes are the durations of the study activities, measured in minutes for each activity. The 6-month semistructured interview will include questions on facilitators, barriers, preferences, and recommendations related to completing study activities.

#### Preliminary Efficacy Outcomes

To prepare for a fully powered trial, we will examine recommended primary and secondary outcomes for the efficacy of the intervention [67-69]. The primary preliminary efficacy outcomes are the number of days of cannabis use, the number of times of cannabis use, and the negative consequences of cannabis use. Days of cannabis use are consistently associated with clinical outcomes, and evidence to date supports the use of this measure to determine cannabis reduction in clinical trials [70]. The number of self-reported days of cannabis use in the past 30 days will be assessed via a TLFB calendar at baseline, 3 months, and 6 months; cannabis use days in the past 14 days will be assessed via TLFB at 3 weeks. For each day with cannabis use, participants will be asked to estimate the time(s) of cannabis use and report their certainty about the time(s) to capture information about changes in total cannabis exposure [70]. The number of self-reported negative consequences of cannabis use in the past 3 months will be measured on the 19-item (yes or no) Marijuana Problems Scale at baseline, 3 months, and 6 months [71].

The secondary preliminary efficacy outcomes will include number of CUD symptoms, amount of THC used, motivation to change cannabis use, psychological distress, cognitive function, and quality of life. Number of CUD symptoms (per the *Diagnostic and Statistical Manual of Mental Disorders*, Fifth Edition [DSM-5]) [72] will be measured by the Composite International Diagnostic Interview–Substance Abuse Module at baseline, 3 months, and 6 months [73]. We consider symptom count to be a secondary outcome because its validity to assess change at 3 and 6 months postintervention in young adults with CUD has not been established. Because participants may change their cannabis use by changing THC potency, we will estimate the amount of THC used from data on the forms and amounts of cannabis collected during the 3-month and 6-month TLFB assessments per international expert consensus recommendations (iCann Toolkit) [69,74]. Number of standard THC units (1 unit=5 mg THC) [75] will be derived from the number of familiar units (juniors, vapes, gummies, etc) multiplied by the amount of cannabis per unit multiplied by the estimated potency [76]. If it is not possible to calculate standard THC units (eg, because complete data are not available), then we will consider the number of familiar units to measure the amount of THC used. We will measure motivation to change at all time points with 0‐10 rulers for readiness, importance, and confidence not to use cannabis [20,53,77]. Functioning will be assessed at baseline, 3 months, and 6 months using validated measures: psychological distress on the Kessler Psychological Scale-6 [78], cognitive function on the PROMIS Cognitive Function v.2.0—Short Form 6a [79], and quality of life on the PROMIS Global Health v1.2 [80].

### Harms

This study confers no more than minimal risk. The study topic could make participants feel uncomfortable or upset, in which case they may skip questions or decide not to continue. Participants could be prompted to answer EMI surveys in situations that may be inconvenient or dangerous, such as during class or while driving; they will be encouraged to use their best judgment about when to complete them. There is a risk of breaches of privacy and confidentiality; participants will be advised to complete study activities in private places where they will not be seen or overheard, and they will be informed that their data will be stored securely. As part of the informed consent process, participants are also advised that the study team will notify their primary care clinician of their enrollment in the study and that, if they meet a clinically informed safety threshold, the clinician will be notified without revealing the participant’s specific responses. Safety thresholds include any of the following self-reported behaviors over the past 30 days: recent binge drinking or heavy alcohol use (male individuals: >5 drinks within 2 h or on any day, or >15 drinks per week; female individuals: >4 drinks within 2 h or on any day or >8 drinks per week), illicit substance use (eg, anything besides alcohol or cannabis to get high), or operation of a motor vehicle within 3 hours of consuming a psychoactive substance. The study team will request clinician confirmation that the notification was received and will follow up as needed. Additionally, confidentiality will be breached in the unlikely event that the participant spontaneously discloses a serious and imminent risk to their safety (eg, suicidality), in which case they will be directly connected with an on-call clinician for standard clinical care. Whether and how the clinician addresses the safety concern with their participating patient will be at the clinician’s discretion and is outside the scope of the study team.

### Ethical Considerations

This paper follows the CONSORT (Consolidated Standards of Reporting Trials) and SPIRIT (Standard Protocol Items: Recommendations for Interventional Trials; Checklist 1) reporting guidelines for randomized trials [81], as well as the guidelines for web-based and mHealth interventions [82]. The study was approved by the hospital Institutional Review Board (IRB-P00049240) and registered on ClinicalTrials.gov (NCT06661031) in October 2024. Protocol amendments will undergo Institutional Review Board approval and will be reported to the National Institute on Drug Abuse as appropriate. The research assistant will facilitate an electronic informed consent process with comprehension checks about study activities, risks, benefits, and confidentiality. Participants will be remunerated up to US $260 in e-gift cards, prorated based on completion of study activities. Payment will be based solely on completion of study activities and will not be contingent on cannabis use, abstinence, or any other outcome. Participation in the study is voluntary, and participants may choose to leave the study at any time. Advisory board members will be offered a US $50 e-gift card per meeting.

### Sample Size

For this pilot feasibility trial, we will enroll 60 patients, whom we will randomize 1:1 to MOMENT-V vs EUC. As our goal is feasibility testing, a sample size calculation is not required. A sample of 60 participants is large enough to describe feasibility constructs. Specifically, for a key measure of trial feasibility, retention, we will be able to estimate a trial retention rate at 3-month follow-up of 80% in a sample of 60 to within a 95% CI of ±10%, that is, 70%-90%, calculated as 1.96 × the square root of [p×(1 p)/n], where p is the percentage retention that we expect to see and n is the intended sample size. Retention efforts will include bimonthly participation reminders, a birthday text, and respectful remuneration.

### Randomization

At the first visit, after completing the baseline assessments, participants will be randomly assigned 1:1 to MOMENT-V vs EUC. Treatment allocation is concealed using a computer-generated urn randomization list via the REDCap (Vanderbilt University) randomization module, which is accessible only to the study biostatistician. Randomization will balance groups by participant factors that may influence study outcomes. Specifically, assignment will be stratified by sex (male vs not male), race (Black or African American vs not Black or African American), cannabis use frequency (daily vs not daily), and recruitment site. Because of the urn randomization algorithm, future assignments cannot be predicted from previous allocations. In addition, study personnel responsible for participant enrollment do not have access to future assignments, preventing prediction of upcoming allocations. The condition will not be masked to participants, study counselors, or research assistants. The condition will be masked to the biostatistician via a numeric binary code.

### Data Collection, Management, and Monitoring

All self-administered surveys will be hosted in REDCap, a HIPAA (Health Insurance Portability and Accountability Act)-compliant platform [83,84]. Validation techniques will be programmed (eg, branching logic, valid numeric ranges, and so on). We will operate under a National Institutes of Health (NIH) Certificate of Confidentiality and use methods to further protect confidentiality and privacy, including assigning a unique numeric study ID to each participant in lieu of storing survey responses with personal information. Data will be exported and stored in a secure, restricted-access location on the hospital’s file network.

The principal investigator will oversee implementation of the study’s data and safety monitoring plan to ensure data integrity and security. Because this is a feasibility trial, there are no plans for interim analyses or stopping rules.

### Data Analysis

#### Quantitative Data

We will examine sociodemographic characteristics and baseline measures to verify that randomization resulted in groups with similar characteristics. We will also use the 2-tailed *t* test (or Wilcoxon-Mann-Whitney test, if data are skewed) and chi-square test (or Fisher exact test) to evaluate equivalence at baseline of the MOMENT-V and EUC groups. We will compute descriptive statistics for baseline sociodemographic characteristics, cannabis use, and related factors.

For the intervention feasibility outcomes, we will calculate the percentage of participants completing the intervention at 6 months and compare it to the benchmark using a chi-square test or Fisher exact test, depending on the data distribution. We will examine sociodemographic and cannabis use determinants of intervention completion using logistic regression models. We will calculate total scores on the acceptability scales and compare them to the benchmarks using a 2-tailed *t* test (or its nonparametric equivalent, the Wilcoxon-Mann-Whitney test, if the data are skewed). Among participants randomized to MOMENT-V, we will summarize each participant’s percentage of days with app engagement using descriptive statistics and compare the percentage of participants completing at least 1 survey per day during the 14-day EMI period to the benchmark. We will examine factors associated with EMI engagement, such as sociodemographic factors and cannabis use characteristics, using multivariable linear or logistic regression. We will use descriptive statistics to summarize ratings of participants’ reports of MET counselor adherence to MI principles and of therapeutic alliance on the WAI-SF, and we will compare the ratings against the benchmarks using a chi-square test (or Fisher exact test).

For the trial feasibility outcomes, we will calculate proportions and 95% CIs for screening, eligibility, enrollment, and retention, and compare them against the benchmarks using chi-square tests. We will also examine the duration of each study activity using descriptive statistics (eg, mean and SD or median and IQR, depending on the distribution and skewness).

We will preliminarily examine the efficacy of MOMENT-V on 30-day cannabis use frequency and on past 3-month negative consequences or problems with cannabis use at 3 and 6 months. To control for potential confounders identified in bivariate analyses of group differences at baseline, we will regress follow-up outcomes on treatment status, adjusting for baseline measures in intention-to-treat analyses. We will conduct analyses using generalized linear mixed-effects models. Models will include the study participant as a random effect and fixed effects for the study arm and potential confounders and covariates such as sociodemographic factors. We will conduct both intention-to-treat and per-protocol analyses to evaluate the robustness of the findings.

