#### Intervention Feasibility Outcomes

The primary outcomes for intervention feasibility include completion, EMI engagement, and acceptability. For intervention completion, we will calculate the percentage of participants assigned to MOMENT-V who complete both MET sessions and any EMI surveys (benchmark: ≥80%). For each MOMENT-V participant, we will determine EMI engagement by calculating the percentage of days (out of a possible 14 d) on which the participant responds to at least 1 EMI survey (benchmark: median ≥80%) [64]. For acceptability, at 6 months we will examine participant satisfaction measured by the Client Satisfaction Questionnaire–8 [65]; each of the 8 items is scored from 1 to 4, and the total score is determined from the sum of the item scores (range of possible total scores, 8‐32), with higher scores indicating greater satisfaction (benchmark: ≥80% of participants with a scale score ≥24, indicating a mean item score of ≥3 out of 4). We will also examine the acceptability of the MET sessions and EMI components using previously-developed scale measures administered following each activity (scales of 11‐12 items with 5-point Likert-type response options from 1=“Strongly Disagree” to 5=“Strongly Agree”); higher scores indicate greater acceptability (benchmark for each scale: ≥80% of participants with a mean item score ≥4 out of 5).

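### Completion, MI adherence and alliance are compared with fixed ≥80% benchmarks by chi-square or Fisher tests in about 30 MOMENT-V participants, which cannot establish whether a benchmark is met

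*Protocol article*

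**What the plan says.** The Intervention Feasibility Outcomes section defines completion as "the percentage of participants assigned to MOMENT-V who complete both MET sessions and any EMI surveys (benchmark: ≥80"%). This is a threshold on a percentage, with everyone assigned to the arm as denominator. The secondary outcomes in the same section have the same form: at least 80% of participants with a mean item score of 4 or more on each MI-adherence scale, and at least 80% with a total WAI-SR score of 48 or more.

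Under Data Analysis, Quantitative Data, the plan for completion is "we will calculate the percentage of participants completing the intervention at 6 months and compare it to the benchmark using a chi-square test" or a Fisher exact test, depending on the data distribution. Participants' ratings of MI adherence and alliance are also compared with their benchmarks by chi-square or Fisher exact test. No significance level or sidedness is given for these comparisons, and nothing says how a test result bears on whether a benchmark is met.

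On size, the Sample Size section says "we will enroll 60 patients, whom we will randomize 1:1 to MOMENT-V vs EUC". It adds "A sample of 60 participants is large enough to describe feasibility constructs" and supports this with one figure, for trial retention: "retention rate at 3-month follow-up of 80% in a sample of 60 to within a 95% CI of ±10"%. No precision is given for outcomes measured only in the MOMENT-V arm.

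**The concern.** The outcome sections ask whether a percentage reaches 80%. The analysis section answers a different question: whether the percentage differs from 80%. Two problems follow.

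- **Form of the test.** Fisher's exact test needs two samples. A fixed benchmark supplies only one, and the exact one-sample counterpart is the binomial test.
- **Information.** Even a valid one-sample test on about 30 people will rarely separate a disappointing rate from a good one. A non-significant result does not show that the benchmark was met, and an arm with a good rate will usually fail to show significance above it.

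The abstract says primary outcomes will be evaluated against a priori benchmarks, and the Conclusions make a large trial conditional on feasibility. Completion is one of the primary outcomes behind that judgement. A reader of Sample Size also sees only the precision for all 60 participants, while these three outcomes come from half of them.

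**Working it through.** **Inputs.** N = 60 at 1:1 (Sample Size), so about 30 in MOMENT-V; urn randomization does not guarantee exactly 30. Benchmark p0 = 0.80 (Intervention Feasibility Outcomes). Two-sided 5% level: my assumption, in line with the 95% CI used in the article.

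**1. The plan's own precision figure.** The formula given is 1.96 × √[p(1−p)/n], "where p is the percentage retention that we expect to see and n is the intended sample size".

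- n = 60, p = 0.80: 1.96 × √(0.16/60) = 0.101, or ±10.1 points. The stated ±10% reproduces.
- n = 30, p = 0.80: 1.96 × √(0.16/30) = 0.143, or ±14.3 points (65.7% to 94.3%). The interval is wider by a factor of √2 = 1.41.
- For ±10 points in one arm, n = 1.96² × 0.16/0.10² = 61.5, so about 62 MOMENT-V participants.
- At an observed 24/30, Clopper-Pearson gives 61.4% to 92.3% and Wilson gives 62.7% to 90.5%.

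**2. Which results the test leaves undecided.** The one-sample chi-square statistic is (x − 24)²/(30 × 0.80 × 0.20) = (x − 24)²/4.8.

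| Completers of 30 | Observed | Chi-square | p (chi-square) | p (exact binomial) |
|---|---|---|---|---|
| 19 | 63.3% | 25/4.8 = 5.21 | 0.022 | 0.036 |
| 20 | 66.7% | 16/4.8 = 3.33 | 0.068 | 0.105 |
| 28 | 93.3% | 16/4.8 = 3.33 | 0.068 | 0.070 |
| 29 | 96.7% | 25/4.8 = 5.21 | 0.022 | 0.020 |

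Both tests fail to reject 80% for 20 to 28 of 30, that is 66.7% to 93.3%. A continuity correction does not change the range.

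The analysed number could be smaller, for example if some participants miss a session and give no rating. The exact binomial range is then 18 to 25 of 27 (66.7% to 92.6%) or 16 to 23 of 24 (66.7% to 95.8%). These two values of n are illustrations only.

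**3. Operating characteristics at n = 30.** The test rejects for x ≤ 19 or x ≥ 29. The threshold rule passes for x ≥ 24, since 24/30 = 80%.

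| True rate | Test rejects 80% | Observed percentage ≥80% |
|---|---|---|
| 70% | 0.270 | 0.160 |
| 75% | 0.108 | 0.348 |
| 80% | 0.036 | 0.607 |
| 85% | 0.051 | 0.847 |
| 90% | 0.184 | 0.974 |

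A true 70% goes unrejected 1 − 0.270 = 73% of the time. A true 90% is shown to be above the benchmark 18% of the time, through x ≥ 29. The simple threshold separates 70% from 90% far better (pass rates of 16% and 97%).

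**4. Timing words.** The outcome section counts all those assigned to MOMENT-V. The analysis section speaks of completion at 6 months. The second MET session comes one week after baseline, and the EMI starts the next day and lasts 14 days, so the intervention ends at about week 3. The two descriptions should be aligned.

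**The case against.** The strongest reply is that the outcome sections already state thresholds, so the tests may be supplementary, and that the pass rule and interval method commonly sit in a statistical analysis plan not shown here. That is fair as far as it goes. But the article does more than leave the matter open: it names tests, and one of them does not apply to a fixed benchmark.

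Several stronger readings are tempting and are not supported:

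- **That all the primary intervention benchmarks are tested this way.** Only completion is. Acceptability gets a t test or Wilcoxon test on total scores. EMI engagement has a median benchmark and no named test.
- **That a non-significant result will count as meeting the benchmark.** No section says so.
- **That ±10% is claimed for the intervention outcomes.** Sample Size ties it to 3-month retention in 60 participants, where it is correct. What can be said is that a general statement of adequacy rests on that one figure.
- **That completion will be computed among 6-month completers.** The wording is loose, but no other denominator is named, and it may only mean when the figure is tabulated.
- **That the problem has one exact size under Fisher's test.** A two-group version would need an invented comparator, which the document does not supply.

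It can also be said that dropping the test is only one defensible choice. A one-sample exact binomial test would be valid in form, though equally weak at this size.

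**Conclusion.** The point stands for three outcomes: completion (primary), and MI adherence and therapeutic alliance (secondary). Fisher's exact test does not suit a fixed benchmark. A two-sided one-sample test leaves everything from 67% to 93% undecided, so it cannot establish whether the rate is at least 80%. These figures assume 30 analysed participants and a two-sided 5% level. The exact range moves little if 24 to 27 are analysed.

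The precision issue is an omission beside a correct figure: about ±14 points at n=30 by the article's own formula, against ±10 for retention. The completion timing is a matter of wording to reconcile; no change of denominator has been shown.

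**What to change.** 1. In Quantitative Data, for completion, MI adherence and alliance, replace the chi-square or Fisher comparison with the threshold already in the outcome section. For example: *the benchmark is met if the observed percentage is at least 80%; the percentage is reported with its Clopper-Pearson (or Wilson) 95% CI.* The same section already plans 95% CIs for the trial-feasibility rates. If a test is kept, make it a one-sample exact binomial test and state its level, its sidedness and its role.
2. State that the completion denominator is all participants assigned to MOMENT-V, and reword the 6-month reference to agree with it.
3. In Sample Size, keep ±10 points for retention (n=60) and add that MOMENT-V-only percentages near 80% have about ±14 points (n=30) by the same formula.

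No participants or data are added. Data collection is projected to end in July 2027, so the wording can be settled before analysis. There are two small costs. A less favourable precision figure is shown. The point-estimate rule is also imperfect: it still passes a true 70% about 16% of the time and a true 75% about 35%, which is why the interval should be reported with it.

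### The acceptability benchmarks are percentages of participants above a cut-off, but the named t and Wilcoxon-Mann-Whitney tests do not assess a percentage and can give the wrong verdict in either direction

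*Protocol article*

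**What the plan says.** Under Intervention Feasibility Outcomes, the Protocol article gives acceptability primary status: "The primary outcomes for intervention feasibility include completion, EMI engagement, and acceptability". The same section sets the benchmarks. For the CSQ-8 it is "benchmark: ≥80% of participants with a scale score ≥24, indicating a mean item score of ≥3 out of 4". For the scales completed after the MET sessions and the EMI it is "benchmark for each scale: ≥80% of participants with a mean item score ≥4 out of 5". Both count participants. Neither sets a target for a mean or median score, and no other section does.

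Under Quantitative Data, the analysis reads "We will calculate total scores on the acceptability scales and compare them to the benchmarks using a 2-tailed" t test, with the alternative described as "its nonparametric equivalent, the Wilcoxon-Mann-Whitney test, if the data are skewed".

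Counselor adherence and therapeutic alliance are secondary outcomes whose benchmarks have the same form (at least 80% of participants above a cut-off). For these, the same section says "we will compare the ratings against the benchmarks using a chi-square test (or Fisher exact test", which is a test on counts.

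**The concern.** The benchmark and the test do not fit each other. A t test on total scores concerns their mean, so 80% cannot be its null value. The only constant it can use is the cut-off itself (24, or an item mean of 4). Whether the mean differs from the cut-off is a separate matter from whether four in five participants reach it.

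The fallback has a further problem. Wilcoxon-Mann-Whitney compares two independent samples, and here there is one group and a constant. The one-sample rank analogue is the signed-rank test, which would not test a proportion either.

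At stake is the verdict on a primary feasibility outcome. The article presents comparison with a priori benchmarks as a strength, and its Conclusions tie a larger trial to the intervention proving feasible. A reader could be told that acceptability was above benchmark when fewer than 80% of participants met the cut-off, or that it was not shown when the benchmark was met.

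**Working it through.** **The plan's own figure.** The article gives no computed figure for acceptability. Its only precision figure is for retention (Sample Size): 1.96 × √(0.8 × 0.2 / 60) = 0.101, which reproduces the stated ±10%.

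**Inputs from the article.** Cut-offs of 24 (CSQ-8, range 8 to 32) and 4 (5-point item mean); benchmark 80%; "we will enroll 60 patients, whom we will randomize 1:1 to MOMENT-V vs EUC", so about 30 in MOMENT-V.

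**Assumptions, not in the article.** Two-sided alpha of 0.05; cut-off used as the t-test null; the means, SDs and shapes below.

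**Step 1. Normal scores, CSQ-8, mean 26, SD 4, n = 30.**
- t = (26 − 24) / (4/√30) = 2.74, p = 0.010, significantly above 24.
- Share at or above 24: Φ((26 − 24)/4) = Φ(0.5) = 69%. With a continuity correction, Φ((26 − 23.5)/4) = Φ(0.625) = 73%.

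**Step 2. Normal scores, 5-point item mean, mean 4.3, SD 0.5, n = 30.**
- t = (4.3 − 4) / (0.5/√30) = 3.29, p = 0.0027.
- Share at or above 4: Φ(0.6) = 73%.

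**Step 3. A constructed data set where the test passes and the benchmark fails.** CSQ-8 scores: nine of 30, seven of 28, five of 26, six of 22, three of 20.
- Sum 788, mean 788/30 = 26.27, SD 3.59, t = 2.27/(3.59/√30) = 3.46, p = 0.0017.
- At or above 24: 9 + 7 + 5 = 21 of 30 = 70% (exact 95% CI 50.6% to 85.3%), so the benchmark is missed.

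**Step 4. A constructed data set where the benchmark is met and the test does not pass.** Twenty scores of 24, five of 25, five of 20.
- Sum 705, mean 705/30 = 23.5, SD 1.63, t = −1.68, p = 0.10.
- At or above 24: 25 of 30 = 83%, so the benchmark is met.

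**Step 5. How often, under a model.** With normal scores and n = 30, the t test becomes significant once the mean lies 2.045/√30 = 0.373 SD above the cut-off, which corresponds to Φ(0.373) = 65% above it. If the true share is 70%, the t test is significant with probability 0.79, while the observed share reaches 80% with probability 0.16. The probability of a significant test with an observed share below 80% is 0.64 for normal scores. It falls to 0.39 for integer CSQ-8 scores with SD 4.

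**Step 6. Sensitivity to shape.** Keep the means and SDs of steps 1 and 2 but use a left-skewed (reflected exponential) shape. The shares become 1 − e^(−1.5) = 78% and 1 − e^(−1.6) = 80%.

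**The case against.** The best reply is that the success criterion is already clear. The benchmark is written as a percentage, the percentage must be computed to apply it, and no stopping rule or formal decision hangs on this p value in a pilot whose goal is feasibility. That limits the damage but does not remove the conflict: the article names the test by which acceptability is compared with the benchmarks, and that test cannot make the comparison. Nor is this a detail left to an analysis plan that is not shown, because the article itself fixes the test.

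A second reply is that the rank test might be meant as a comparison of arms. The text says the scores are compared with the benchmarks, and EUC participants receive no MET or EMI to rate.

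A third reply concerns size, and it stands. The means and SDs are assumed. A normal curve also ignores the scale limits: with the assumed values, about 7% of CSQ-8 scores would exceed 32 and about 8% of item means would exceed 5. The article itself anticipates skew, and step 6 shows that skew can almost close the gap.

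Two stronger readings are tempting. A reader might infer that the t test is simply an easier hurdle. Step 4 shows that it can also be harder, so only a different question can be claimed. A reader might also infer that the CSQ-8 percentage will be inflated because drop-outs are left out, since "at 6 months we will examine participant satisfaction measured by the Client Satisfaction" questionnaire. The article does not say how non-responders are handled, and a condensed article commonly leaves that to the full plan. The point would also not be the same for the MET and EMI scales, which follow each activity. No finding is made on it.

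**Conclusion.** The plan is wrong as written on this point. The benchmarks and the named analysis for a primary outcome do not match, no section reconciles them, and the same analysis section uses a count-based test for secondary outcomes with benchmarks of the same form. This conclusion needs no distributional assumption: the two constructed data sets show that the wrong verdict is possible in both directions.

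How often it would happen cannot be stated from the article. The figures of 69% to 73% at or above the cut-off with p = 0.010 or smaller rest on assumed normal scores, means and SDs. They are illustrations, not estimates for this trial.

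**What to change.** In the Quantitative Data section, remove the t and Wilcoxon-Mann-Whitney tests for acceptability. For each scale, report the number and percentage of MOMENT-V participants at or above the cut-off (24 for the CSQ-8; item mean 4 for each MET and EMI scale) with a Wilson or Clopper-Pearson 95% CI, and judge that percentage against 80%. If a test is wanted, use an exact one-sample binomial test against 80%. Keep mean or median scores as description only. If the analysis plan carries the same wording, change it there too.

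The change needs no new data and can be made before analysis, since data collection is projected to run to July 2027. There are two costs. Reported acceptability may look less favourable. The interval will also be wide: by the article's own formula with 30 participants, 1.96 × √(0.8 × 0.2 / 30) = 0.143, or about ±14 percentage points around 80%.

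### Covariates for the efficacy models are to be picked from baseline tests between the randomized arms, so adjustment follows chance imbalance and the randomization factors are not secured in the model

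*Protocol article*

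**What the plan says.** Under Data Analysis, Quantitative Data, the article plans t tests (or Wilcoxon-Mann-Whitney) and chi-square tests (or Fisher exact) "to evaluate equivalence at baseline of the MOMENT-V and EUC groups". No significance threshold and no list of variables is given.

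The efficacy paragraph then applies these comparisons: "To control for potential confounders identified in bivariate analyses of group differences at baseline, we will regress follow-up outcomes on treatment status", with the qualification "adjusting for baseline measures in intention-to-treat analyses". The models are generalized linear mixed-effects models. "Models will include the study participant as a random effect", together with "fixed effects for the study arm and potential confounders and covariates such as sociodemographic factors". The targets are 30-day use frequency and "past 3-month negative consequences or problems with cannabis use at 3 and 6 months".

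The Randomization section describes an urn procedure intended to balance factors thought likely to affect outcome: "assignment will be stratified by sex (male vs not male), race" (Black or African American or not), "cannabis use frequency (daily vs not daily), and recruitment site". The efficacy paragraph names none of these four as a required model term, and it does not mention site at all.

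**The concern.** The selection rule is stated; it is not a detail left to another document. It has two faults.

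First, allocation is random and concealed, so any baseline difference between arms is due to chance. A p-value for that difference says nothing about whether the variable predicts outcome, and prognostic strength is what decides whether adjustment helps. A non-significant test at this sample size is also weak evidence of similarity and cannot establish equivalence.

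Second, the rule works against the variables the investigators themselves consider prognostic. Balancing on sex, race, daily use and site makes a significant baseline difference on them less likely, so a rule that selects on differences tends to pass them over.

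The stake is the quality of the efficacy estimates meant to inform the fully powered trial: their precision, whether their standard errors are right, and whether the adjustment set is fixed before the data are seen.

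**Working it through.** **The plan's own figure.** The only design calculation is in Sample Size: 80% retention among 60, to within ±10%. Check: 1.96 × √(0.8 × 0.2 / 60) = 0.101, giving 69.9% to 90.1%. It reproduces, but it does not bear on the efficacy model, for which no figure is stated.

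**Inputs from the article.** 60 participants, 1:1, so 30 per arm; four randomization factors; two efficacy time points.

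**Assumptions, not in the article.** Test level 0.05 (also 0.10 and 0.20); 5 to 20 independent baseline variables; covariate–outcome correlation 0.3 to 0.7; a continuous outcome.

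**1. What the tests can miss.** The standard error of a standardized mean difference is √(2/30) = 0.258. The two-sided 5% limit is 1.96 × 0.258 = 0.506, so an observed imbalance of up to about 0.5 SD is non-significant.

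**2. What the tests flag by chance.** P(at least one flag) = 1 − (1 − α)^k.

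| Variables k | α | P(at least one) |
|---|---|---|
| 5 | 0.05 | 23% |
| 10 | 0.05 | 40% |
| 15 | 0.05 | 54% |
| 20 | 0.05 | 64% |
| 10 | 0.10 | 65% |
| 10 | 0.20 | 89% |

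**3. Cost of selecting rather than prespecifying.** This was simulated with 6,000 trials at 30 per arm, no true effect and one prognostic covariate. The baseline test at 0.05 selected the covariate in 4.5% to 5.0% of trials, as it must under randomization.

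| Correlation with outcome | SE, prespecified | SE, selected by test | Type I error, prespecified | Type I error, selected |
|---|---|---|---|---|
| 0.3 | 0.248 | 0.255 | 4.8% | 4.5% |
| 0.5 | 0.227 | 0.250 | 5.2% | 4.4% |
| 0.7 | 0.187 | 0.243 | 4.8% | 3.6% |

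The SE columns give the spread of the estimate across trials. The ratios are 1.03, 1.10 and 1.30. The loss applies to a covariate not already in the model for another reason.

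**4. Cost of leaving out a balanced factor.** If a perfectly balanced factor explains a share R² of outcome variance and is omitted, the reported standard error is too large by 1/√(1 − R²). The actual type I error is then about 2 × Φ(−1.96/√(1 − R²)).

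- R² = 0.10: 1.96/0.949 = 2.07, about 3.9%; simulated 3.6%.
- R² = 0.25: 1.96/0.866 = 2.26, about 2.4%; simulated 2.5%.
- R² = 0.50: 1.96/0.707 = 2.77, about 0.6%; simulated 0.6%.

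With the factor included, the simulated rates were 4.5% to 5.0%. Urn randomization balances less tightly than this, so these figures are towards the extreme.

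**5. Why the time terms are worth confirming.** In a simulated mixed model with invented effects of −0.6 at 3 months and 0 at 6 months, a model with arm but no visit terms returned one value, −0.27. Adding visit and arm-by-visit returned −0.58 and +0.03. This shows only what such a model would do; it is not evidence that the trial will use it.

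**The case against.** Four points on the other side deserve weight.

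*The model does not clearly omit the randomization factors.* A reader might infer that it does, or that they enter only if they happen to differ. The wording does not support that. Covariates are named alongside confounders and the list is open. Sex and race are sociodemographic, and daily use can fall under the adjustment for baseline measures. What stands is narrower: none of the four is committed to, and site is not mentioned.

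*The article does not say that visits will be pooled.* A reader might infer from the listed terms that 3- and 6-month effects cannot be separated. But both times are named as targets, the list of terms is not said to be complete, and Results refers to a statistical plan that is not shown here. Time terms are commonly left to such a plan, so their absence is a matter to confirm and not a fault.

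*Not all the gain from adjustment is new.* At an assumed correlation of 0.6 one could claim 1/(1 − 0.6²) = 1.56 times the sample for the fix. That credits it with adjustment for baseline measures the article already states. The true increment is what the remaining factors add beyond baseline, and the documents give no figure for it.

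*The consequence is limited.* Efficacy is labelled preliminary, the trial makes no power claim for it, and the primary outcomes are feasibility measures. This stands in full.

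None of these points defends choosing covariates by baseline tests.

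**Conclusion.** The concern holds for the selection rule. The article states that confounders are identified from differences between randomized arms, and that rule selects on chance. At an assumed 5% level it leaves imbalances up to about 0.5 SD unflagged and flags at least one of 5 to 20 independent variables with probability 23% to 64%.

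The harm is threefold: lost precision (standard errors 3% to 30% larger than under prespecified adjustment for assumed correlations of 0.3 to 0.7), tests that are conservative and not inflated, and an adjustment set unknown until the data are seen, which may differ between outcomes. These sizes rest on a continuous outcome and on a covariate not otherwise in the model. The randomization factors are best described as not secured. The feasibility outcomes are unaffected. This should be corrected, but it does not threaten the trial's main purpose.

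**What to change.** Drop baseline significance testing as the means of choosing covariates, and present baseline characteristics by arm descriptively.

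Prespecify for every efficacy model, whatever the baseline table shows:

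- the baseline value of that outcome;
- sex, race and daily use as defined for randomization, leaving daily use out where baseline days of use already covers it;
- recruitment site as numbers allow. Setting and Recruitment starts with two clinics and adds others as needed, so small sites may have to be pooled under a rule written in advance.

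Confirm in the statistical plan that the models contain visit (3 and 6 months) and arm-by-visit terms, with arm contrasts and 95% confidence intervals reported at each time.

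The cost is wording and a few degrees of freedom. With two clinics, the adjustment uses at most five (baseline value, sex, race, daily use, site: 1 + 1 + 1 + 1 + 1), and the time terms add two. No new data are needed. Data collection is projected to run to July 2027, so the change can be made before the outcome data are complete.
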